### Case number calculation / sample size

With regard to the changes in the primary outcome, we assume that both groups (the CG and IG) will have improved in a similar way at the end of the MKP. According to our assumptions, the effect of the CG during the subsequent period will approach the starting level again, while the positive changes in the IG will stabilize or even increase slightly. To estimate the required sample size, we have referred to the results of existing studies on the influence of physical activity on quality of life (PDQ-8) in PD patients. For the effect determination, the data of Ebersbach et al. [46], Morris et al. [47] and Nadeau et al. [10] are being consulted. In Ebersbach et al., the quality of life over a 4-month course showed effect sizes of average magnitude (ES = 0.47) for patients who underwent physical training (Nordic walking), whereas there was no change in the CG. Morris et al. also report a significantly improved quality of life, with a mean effect size of ES = 0.45, after muscle training over a 3-month span. In their controlled study on the effect of intensive treadmill training (speed and incline) on quality of life, Nadeau et al. found an effect size of ES = 0.73 over a 6-month course; for simple treadmill training, they found an effect strength of ES = 0.21. In the CG, the quality of life did not change. For the calculation of the number of cases, we assume that participation in the tablet-based training programme (IG) will lead to clinically relevant positive effects (t_0_ vs. t_2_ ES = 0.40) on quality of life (PDQ-8) 9 months after the end of MKP. In contrast to the IG, there will be no changes in the CG at t_2_. To demonstrate differences between the IG and CG 9 months after MKP on the order of at least ES = 0.4 with two-sided testing at α = 5% and a power of 80%, a group size of *N* = 100 net is required for each IG and CG. We expect only a moderate dropout rate of 25% among patients after MKP due to their attachment to the clinic. Thus, to be able to evaluate N = 100 patients per group, 133 participants per study group must initially be included. Approximately 120 PD patients participate in the MKP per quarter at the partner clinic. Based on the defined inclusion and exclusion criteria, we expect 70 patients per quarter to be included in the study. The recruiting of the CG and IG will take place over a period of nine months each. Taking into account a rate of study refusal of 25%, the targeted number of cases in the clinic can be recruited within this time frame.

## Statistical methods

### Quantitative analyses

Repeated analysis of variance will be used to analyse the longitudinal data, a contingency table analysis will be used for nominal and ordinal parameters, and chi-square tests and t-tests will be used for subgroup analysis. Subgroup analyses are planned for age, sex and education (boundaries: high vs. low). For the evaluations only complete cases are used. The analyses will be performed using the statistics programme SPSS 22.0.

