### Intervention

The planned training programme is based on the HAPA model [15], which focuses in particular on the factors of intent formation and concrete implementation of the established health behaviour. In practice, the patient-centred 5-A-model (assess, advise, agree, assist, arrange) will also be used as an evidence-based framework for health behaviour interventions [16] to increase patients’ self-management skills and support behavioural change [17]. The training programme for PD patients is developed as an application (app). This app will be installed on a tablet, which will be given to the patients of the IG at the beginning of the MKP. The app contains videos with verbal instructions and explanations for all the physically activating exercises taught in the MKP. These exercises are available in different degrees of difficulty and promote endurance, strength and balance. Other physical activities, such as Nordic walking, Tai Chi or dancing, are also suggested. When the patient activates a specific exercise or physical activity, they may also enter personal notes.

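### The 80% power is for a two-group comparison of PDQ-8 at 9 months, but the named repeated-measures ANOVA has no primary term or contrast, and its default omnibus tests are not that comparison

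*Protocol article*

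**What the plan says.** The sample size section of the Protocol article (Case number calculation / sample size) sets out the expected course. For the end of the inpatient treatment (MKP): "we assume that both groups (the CG and IG) will have improved in a similar way at the end of the MKP". After that the CG is expected to drift back to its starting level while the IG holds its gain.

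The effect is worded in two ways. As a change, the programme "will lead to clinically relevant positive effects (t_0_ vs. t_2_ ES = 0.40) on quality of life (PDQ-8"), and for the controls "In contrast to the IG, there will be no changes in the CG at t_2". As a group difference, the stated purpose of the calculation is: "To demonstrate differences between the IG and CG 9 months after MKP on the order of at least ES = 0.4". The significance level is 5%, two-sided, and the target power is 80%. The section concludes that "a group size of *N* = 100 net is required for each IG and CG". Section A (quantitative measures) and Table 1 have PDQ-8, the primary outcome, collected at t0, t1 and t2.

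The section Quantitative analyses then states: "Repeated analysis of variance will be used to analyse the longitudinal data". It restricts the evaluations to complete cases. It does not say which effect or contrast carries the primary conclusion.

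On timing, the Intervention section says the app is installed on a tablet "which will be given to the patients of the IG at the beginning of the MKP". Two seminars and an individual planning appointment also fall within the MKP, so the intervention has begun before t1.

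**The concern.** The sample size and the analysis are described as if they belonged together, but nothing connects them. A repeated-measures ANOVA of a three-visit outcome in two groups produces two omnibus tests that involve group:

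- **The group main effect** averages the difference over t0, t1 and t2. A difference expected only at t2 is cut to a third.
- **The group-by-time interaction**, on 2 degrees of freedom, responds to any departure from parallel profiles, whether it arises at t1 or at t2.

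Neither is the 9-month comparison for which the trial was sized. If either is read as the primary result, the p-value may answer a different question, and its power is not the stated 80% except by coincidence. Leaving the term open also allows several p-values to compete for the primary conclusion. This matters more here because patients are unblinded, the outcome is self-reported, and the groups are recruited one after the other without randomisation.

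**Working it through.** **Inputs from the Protocol article.** 100 evaluable per group; effect 0.4; two-sided 5%; 80% power; no difference expected at t1; CG unchanged from t0 to t2. With equal baselines, the implied IG–CG differences at (t0, t1, t2) are (0, 0, 0.4) in SD units.

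**Assumptions, not in the document.** Equal SD at each visit and one common correlation ρ between visits, taken over 0.3 to 0.7. The effect 0.4 is first read in SDs of scores.

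**1. The plan's own figure.** For a two-sample t-test at t2 the noncentrality is 0.4 × √(100/2) = 2.83 on 198 df, giving 80.4% power. The normal-approximation formula needs 99 per group. The stated 100 is therefore right for that test, and ρ plays no part in it.

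**2. The ANOVA tests and the alternatives, 100 per group.** The noncentrality λ is n/2 = 50 times the squared effect over its variance:

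- Group main effect: λ = 50 × (0.4/3)² / [(1+2ρ)/3], F(1,198)
- Group-by-time: λ = 50 × 0.16 × (2/3) / (1−ρ), F(2,396)
- t0-to-t2 change contrast: λ = 50 × 0.16 / [2(1−ρ)], F(1,198)
- t2 adjusted for t0: λ = 50 × 0.16 / (1−ρ²), F(1,197), equal baselines

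| Test | ρ = 0.3 | ρ = 0.5 | ρ = 0.7 |
|---|---|---|---|
| Group main effect | λ 1.67, 25% | λ 1.33, 21% | λ 1.11, 18% |
| Group-by-time, 2 df | λ 7.62, 69% | λ 10.67, 84% | λ 17.78, 97% |
| t0-to-t2 change contrast | λ 5.71, 66% | λ 8.00, 80% | λ 13.33, 95% |
| t2 adjusted for t0 | λ 8.79, 84% | λ 10.67, 90% | λ 15.69, 98% |
| t2 alone, unadjusted | 80% | 80% | 80% |

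The interaction reaches 80% at ρ ≈ 0.45. For 80% power it needs 128, 92 and 55 per group at ρ = 0.3, 0.5 and 0.7. The main effect would need 471, 589 and 707.

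**3. The scale of the effect.** If 0.40 is in SDs of change, the score-scale difference is 0.4 × √[2(1−ρ)]. Then λ for the change contrast is 50 × 0.16 = 8 at every ρ, and power is 80% throughout. The interaction then has 84% throughout.

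**4. Specificity to 9 months.** With differences (0, d, 0), that is, at t1 only, the interaction has λ = 50 × d² × (2/3)/(1−ρ). For d = 0.3 it is significant in 58% of trials at ρ = 0.5 (λ = 6) and 81% at ρ = 0.7 (λ = 10). At ρ = 0.3 the figure is 44% (λ = 4.29). The t0-to-t2 contrast stays at 5%.

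**The case against.** The strongest reply is that the analysis sentence is general. It covers every longitudinal outcome, including several measured only at t0 and t2, for which group-by-time already is the 1-df t0-to-t2 comparison. It names no ANOVA term, so a reader who infers that the planned test cannot target t2, or that the 80% is simply wrong for it, goes further than the text. The sample size section frames the hypothesis as a t0-to-t2 change. A contrast within the ANOVA tests exactly that, with 80% power at ρ = 0.5, or at any ρ if 0.40 is in SDs of change. This stands.

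It is also fair that the 18–25% belongs to a main effect that nobody has proposed as the primary test, and that the interaction has at least 80% power once ρ is about 0.45. An inference that the trial is underpowered in general is therefore not supported. The t1-only scenario departs from the protocol's own assumption of similar improvement by the end of the MKP. It shows what the omnibus test can respond to, not what is expected. Nor is baseline ignored, since an ANOVA that includes t0 uses it in the interaction, and the Limitations section foresees covariates or propensity matching if the groups differ.

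Finally, a condensed article may leave the choice of contrast to a fuller document. That tempers the point but does not remove it: the article states a specific N, power and time point beside a specific method whose default output for PDQ-8 is not that test.

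**Conclusion.** The point holds in a limited form. The N of 100 and the 80% power are correct for a two-group comparison at 9 months. The method named for the longitudinal data does not say which effect or contrast is primary, and for PDQ-8 at three visits its default omnibus tests are not that comparison. Depending on the term read and on an unstated correlation, their power runs from about 18% to 97%, and the 2-df test is not specific to 9 months. This rests on the protocol's expected profile, equal variances and a common correlation of 0.3 to 0.7; other correlation patterns would move the figures. No general power loss is shown, and no error in the sample size arithmetic for the t2 comparison. What is shown is an open choice of primary test, which a single pre-specified 9-month contrast settles.

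**What to change.** In Quantitative analyses, before the data are analysed:

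- Name one primary test: the IG minus CG difference in PDQ-8 at t2, adjusted for t0 PDQ-8, 1 df, two-sided 5%, with a 95% confidence interval. ANCOVA does this, as does the t2 contrast of a mixed model with t0 as covariate and t1 and t2 as outcomes. Do not use t1 as the baseline, because the intervention has started by then.
- Report the group difference in the t2 minus t0 change as a sensitivity analysis. The groups are sequential rather than randomised, so the adjusted and change-score analyses can answer different questions if baselines differ.
- Keep t1 and the overall time profile as secondary.
- State whether the effect of 0.40 is in SDs of scores or of change, and give the power for the named contrast with the correlation assumed.

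The cost is a few sentences, with no extra patients or data. On the score scale and with balanced baselines, the adjusted comparison has 84%, 90% and 98% power at ρ = 0.3, 0.5 and 0.7 with the planned 100 per group. The one small downside is that the primary and sensitivity results may disagree under baseline imbalance, so the plan should say in advance that both will be shown and which is primary.

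### The tests named for the subgroup analyses contain no group-by-factor interaction, so they cannot show that the intervention effect differs by age, sex or education

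*Protocol article*

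**What the plan says.** The section on quantitative analyses assigns methods by purpose. For the course over time: "Repeated analysis of variance will be used to analyse the longitudinal data". For subgroups: "chi-square tests and t-tests will be used for subgroup analysis". The factors follow: "Subgroup analyses are planned for age, sex and education (boundaries: high vs. low"). The analysis set is also fixed: "For the evaluations only complete cases are used".

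The article names no interaction term or test of heterogeneity, and attaches no exploratory label to the subgroup results. The sample size section covers the overall comparison only. Its target reads: "To demonstrate differences between the IG and CG 9 months after MKP on the order of at least ES = 0.4". At the usual two-sided 5% level and 80% power, the section arrives at this requirement: "a group size of *N* = 100 net is required for each IG and CG".

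The Limitations section foresees that differences in patient characteristics between the two groups will be taken into the analyses, by covariates or by propensity score matching. It does not mention subgroups.

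**The concern.** A subgroup analysis is normally read as an answer to the question of who benefits more. A two-sample t-test or a chi-square test cannot answer it. Run within a subgroup, it compares IG with CG there. Run between subgroups, it compares, say, older with younger patients. On neither reading is the difference between two intervention effects tested.

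The risk arises when subgroup results are set side by side. With about half the sample in each subgroup, a test that is significant in one half and not in the other is a common chance result, even if the effect is the same in both. A statement that the programme works in one kind of patient and not in another could then rest on noise.

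A second point concerns adjustment. CG and IG are recruited one after the other, and the Limitations section keeps covariates in reserve for differences between them. A plain t-test has no place for covariates.

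**Working it through.** **Inputs.** From the sample size section: ES = 0.4, two-sided α = 5%, power 80%, 100 evaluable per group, 25% dropout. From the quantitative analyses section: three factors with two levels each. Assumed, because the article does not give them: subgroup shares (50/50, with 40/60 and 30/70 as a range), equal shares in both groups, factors unrelated to one another, and a common effect of 0.4 SD in all subgroups.

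**1. The plan's own figure.** n per group = 2 × (1.960 + 0.842)² / 0.4² = 98.1, so 99 by the normal approximation. The t-based calculation gives 99.1, so 100. Power at 100 per group is 80.4% (t). Dropout: 100 / 0.75 = 133.3, stated as 133. The stated size is reproduced for the overall contrast.

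**2. Power within one half (50 per arm).** Expected z = 0.4 × √(50/2) = 2.0. Power ≈ Φ(2.0 − 1.96) = 51.6% (normal), or 50.8% (t).

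**3. One subgroup significant and the other not, same true effect in both.** Probability = p₁(1 − p₂) + p₂(1 − p₁), with t-based powers:

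| Split | p₁ | p₂ | Discordant |
|---|---|---|---|
| 50/50 | 0.508 | 0.508 | 0.50 |
| 40/60 | 0.424 | 0.584 | 0.51 |
| 30/70 | 0.332 | 0.652 | 0.55 |

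**4. At least one discordant pair among three factors.** The product rule, 1 − 0.5³ = 87.5%, does not apply: all three factors split the same 200 patients, so the results are correlated. Simulation with three unrelated factors on the same data gives 75% at 50/50 and about 81–82% at 30/70.

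**5. No effect at all.** Six tests at 5% would give 1 − 0.95⁶ = 26% if independent. They overlap for the same reason. Simulation gives at least one significant subgroup in about 20–21%.

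**6. Interaction test instead.** For a 50/50 split, the standard error of the difference between the two effects is √(2/50 + 2/50) = 0.283 SD.
- False finding of a difference: 5% per factor (5.2% simulated). Across three factors: 1 − 0.95³ = 14.3% (14.5% simulated).
- Power for a true difference of 0.4 SD: 0.4 / 0.283 = 1.414; Φ(1.414 − 1.96) ≈ 29%.
- Power for 0.8 SD: 0.8 / 0.283 = 2.828; Φ(2.828 − 1.96) ≈ 81%.
- Size for 80% power at 0.4 SD: (1.960 + 0.842)² × (2/0.5 + 2/0.5) / 0.4² = 392.4, so 393 per group.

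**The case against.** The strongest reply is that much of the harm is inferred. The article does not say that IG and CG are tested separately in each subgroup, that p-values will be contrasted, or that a claim about differential benefit will follow. Its aims and sample size contain no subgroup hypothesis. A reader might infer that the trial will report who benefits on the strength of such contrasts; the text does not say so. This stands, and it makes the figures in steps 2 to 5 conditional on that use. It does not rescue the method, because the alternative reading (high against low) does not test effect modification either.

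A reader might also infer that the subgroup t-tests ignore baseline and carry the full confounding of the sequential design. The article does not support that. The outcome of the t-tests is not stated and could be the change from t0 to t2, which uses baseline. The Limitations section also promises adjustment, and propensity score matching could precede a t-test. What remains is narrower: covariate adjustment, one of the two routes named, does not fit into a plain t-test.

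Dichotomisation is a lesser matter. Sex is binary in any case, and education may be recorded in levels. Only age clearly loses information.

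Finally, a journal article leaves detail to the full plan. But here a method is named for the purpose, and the named method is unsuitable, so this is not a complaint about missing detail. Low interaction power also stands: subgroup findings remain exploratory after the change.

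**Conclusion.** The point holds as follows. The tests assigned to the subgroup analyses cannot show that the intervention effect differs by age, sex or education, however they are run. If they are run within subgroups and contrasted, an apparent difference arises where none exists in about 50–55% of trials per factor (50/50 to 30/70 split) and in about 75–82% for at least one of three factors. An interaction test brings this to about 5% per factor and about 14% across three.

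These figures assume a common effect of 0.4 SD, 100 complete cases per group and unrelated factors; the subgroup shares are not in the article. The higher values of 87% (a discordant pair) and 26% (a significant subgroup under no effect), which a reader might obtain by multiplying probabilities, overstate the risk because the factors divide the same patients.

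The primary comparison is untouched. The change should be made because it protects secondary statements at almost no cost.

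**What to change.** Replace the subgroup clause in the quantitative analyses section with:

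> Effect modification by age (continuous), sex and education is examined with a group-by-factor interaction term in the primary longitudinal model, with the same adjustment for group differences as in the main analysis. Subgroup estimates with 95% CI are shown descriptively and labelled exploratory, without within-subgroup significance tests.

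In a repeated-measures model, the term to cross with the factor is the one that carries the IG–CG contrast in change over time.

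Cost: one or two sentences, no new data and no change in sample size. The downside is that interaction power is low, about 29% for a difference of 0.4 SD at the planned size, so a non-significant interaction must not be read as evidence of equal effects. Subgroup statements will be more cautious than the present wording allows.

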During MKP, after completing an exercise, patients record the repetition rate or duration of the exercises on the tablet and rate them with regard to well-being, effort and fun. During the MKP, patients also take part in two patient-centred seminars. The first is primarily for acquiring knowledge and motivation. The focus of the second seminar is on preparing for everyday life at home. Each patient considers personal barriers that may arise in daily routine and strategies to overcome those barriers. Possible action alternatives are defined and entered into the app. At an individual appointment at the end of the MKP, patients plan their personal home training programme on the tablet, with the support of the physiotherapist. The patient chooses exercises that match their abilities, needs and preferences. The physiotherapist assists the patient in putting together their individual training programme: she gives advice regarding the selection of the activating exercises, the degree of difficulty and the number of repetitions. The exercises and the adaptation of the exercises over the weeks are based on the learning method of behaviour shaping in operant conditioning. Here, the desired motor behavioural goal is achieved by gradually increasing effort and difficulty, practising repetitive exercises and constantly adjusting the exercises to the patient’s level of ability. Shaping has proven to be an effective training method in neurological movement disorders [18]. Patients will set a date and time for at least three 30-min sessions of physiotherapy exercises and for at least one physical activity per week for the next three weeks at home. The app displays this individually scheduled training programme in a calendar function. At home, the app reminds patients through a sound signal and/or push notification to execute their exercise programme at the scheduled time. Postponing a session (e.g., due to temporary aggravation of motor impairments, so-called off periods) is possible. The videos offer visual support in the execution of the selected exercises. After completing a scheduled training session, patients will document whether the given repetition number or duration was achieved and whether there were problems performing the exercises, and they also rate the activity in terms of well-being, effort and fun. After the end of the MKP, the data are transferred automatically from the app into an administration panel called “Cockpit” at the clinic. There, the supervising physiotherapist can monitor adherence by controlling the patient’s documentation regarding the execution of the exercises and activities, the repetition number, incomplete video viewings, etc. To permit this, the app transmits the gathered statistics for the activities performed by the patients at regular intervals. To be independent of wireless Internet access, transmission takes place via the mobile network. Based on these data, the physiotherapist provides feedback by phone and adjusts the training programme at regular intervals after the end of the MKP. Because PD patients are prone to small movement amplitudes during exercise that they cannot perceive and therefore cannot correct by themselves, regular correction by experts is required. For this reason, in addition to the telephone contacts, the patients visit the clinic four times after their MKP. Travel expenses to the clinic will be financially reimbursed. If patients have any further need for assistance between those pre-defined appointments, they can contact their physiotherapist at the hospital. Regular, attentive care and feedback from the physiotherapist promote long-term adherence [19].

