### A: quantitative measures

To examine the long-term effects, we will conduct a monocentric, quasi-randomized longitudinal study with three measurement times: at the beginning (t_0_) and end of the MKP (t_1_) and 9 months after the MKP (t_2_). Recruitment of control group (CG) and intervention group (IG) will be performed in a sequential order, i.e., initially, all patients that are being admitted to our partner clinic during the first recruitment period will be consecutively assigned to the CG (treatment as usual) until the desired number of cases has been reached. The second recruitment period starts after the recruitment of the CG is completed. Patients that are subsequently arriving at the partner clinic for their MKP will be consecutively assigned to the IG until the desired number of cases has been reached. Neither participants nor the study personnel or care providers at the clinic will be blinded. To control the equal treatment of IG and CG during the MKP, all treatment measures that the groups receive will be continuously documented by means of an EDP-based treatment plan. All patients will complete a written questionnaire using standardized, validated instruments. Table 1 shows the core set of instruments to be used in the study.

**Table 1 Tab1:** Core set of instruments used in the quantitative part of the study

Dimensions	Instruments	t_0_	t_1_	t_2_
Primary Outcome				
Quality of Life	PDQ-8 [24]	●	●	●
Secondary Outcomes				
Participation Restrictions	IMET [24]	●		●
Fear of Falling	FES-I [25]	●	●	●
Sleep Disorder	PDSS-2 [29]	●	●	●
Anxiety/Depression	PHQ-4 [31]	●	●	●
Comorbidity	SCQ-D [26]	●		●
Pain	Single Items [27]		●	
Performance Capability	Single Items [28]	●		●
Physical Activity	Federal Health Survey [29]	●		●
Moderating Variables				
Body Height, Weight	Single Items	●		●
Use of Health Services (Medical and Therapeutic Treatments, Hospital Stays, Medication, etc.)	Single Items	●		●
Sociodemographic Data	Single Items [30]	●		●

t_**0**_ = baseline/right before MKP; t_**1**_ = 3-week follow-up/right after MKP; t_**2**_ = 9 months after t_**1**_

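### Restricting all quantitative evaluations to complete cases, with 25% dropout expected and unequal contact between arms, leaves the 9-month comparison open to attrition bias that an analysis using the t0 and t1 data could reduce.

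*Protocol article*

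**What the plan says.** The Quantitative analyses section fixes both the method and the analysis set. The method: "Repeated analysis of variance will be used to analyse the longitudinal data". The analysis set: "For the evaluations only complete cases are used". No other analysis set, imputation or missing-data sensitivity analysis is named there. The rule is written out, so it is not a detail left to a fuller document.

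The sample size section plans for loss: "We expect only a moderate dropout rate of 25% among patients after MKP due to their attachment to the clinic". It gives one rate for both groups and inflates accordingly: "Thus, to be able to evaluate N = 100 patients per group, 133 participants per study group must initially be included".

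Table 1 places the primary outcome, PDQ-8, at all three times (t0 at the start of MKP, t1 at its end, t2 nine months later).

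The Intervention section gives the intervention group app reminders, regular phone feedback and reimbursed travel, and says that "in addition to the telephone contacts, the patients visit the clinic four times after their MKP". It also asks that group for at least three 30-minute exercise sessions and one further activity a week. The control group has treatment as usual. Both groups complete the same written questionnaire at the same times. The Limitations section plans covariates or propensity matching if patient characteristics differ between the two recruitment periods. It does not mention loss to follow-up.

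**The concern.** A patient without t2 drops out of the primary comparison altogether, including the t0 and t1 scores already collected. The groups compared at nine months are then defined by who stayed, which is decided after allocation and which the intervention itself can influence. The article ties retention to patients' attachment to the clinic. After MKP that attachment is maintained by trial contact in one arm only, while the training burden also falls on that arm. Retention in the intervention group could therefore be better or worse than in the control group, and it could select different patients.

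Inflating 100 to 133 protects power but does nothing about bias. The comparison is also unblinded and between sequential cohorts, so attrition would add a second source of selection to the one that the Limitations section already recognises.

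**Working it through.** **1. The plan's own figures.** Inputs from the sample size section: effect size 0.4, two-sided 5%, power 80%, dropout 25%.
- Normal approximation: n = 2 × (1.960 + 0.842)² / 0.4² = 98.1, so 99 per group. The t-test solution is 99.08, so 100. The stated 100 reproduces.
- Inflation: 100 / 0.75 = 133.3, stated as 133; 133 × 0.75 = 99.75. The rounding is trivial.

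**2. What is left out.** 133 × 0.25 = 33 patients per arm. With two visits and two arms, that is 33 × 2 × 2 = 132 PDQ-8 records out of 133 × 2 × 2 + 100 × 2 = 732 expected, if all dropout occurs after t1. This applies to outcomes measured at t1 (PDQ-8, FES-I, PDSS-2, PHQ-4). For IMET, measured at t0 and t2 only, dropouts contribute only a baseline value.

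**3. How large the bias could be.** The article gives no correlations, no dropout by arm and no dropout mechanism, so these are assumptions: outcome SD 1, true intervention-minus-control difference -0.40, equal correlation between visits, and logistic dropout after t1 with log-odds 0.7 per SD of the driving score. The estimand is the group difference in the t0-to-t2 change. Scores were simulated with 300,000 patients per arm. The table uses correlation 0.5 except in the last row.

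| Dropout scenario | Complete-case estimate | Bias (SD) |
|---|---|---|
| 25% in both arms, same mechanism | -0.40 | 0 |
| Driven by t1 alone, any split | -0.40 | 0 |
| 20% intervention, 30% control, same mechanism | -0.43 (t0-driven) or -0.37 (change-driven) | 0.03 |
| 25% in both arms, one arm only, log-odds 0.35 | about -0.36 or -0.44 | about 0.04 |
| 25% in both arms, dependence on t0 or on t0-t1 change in one arm only | about -0.32 or -0.48 | about 0.08 |
| 35% vs 15%, same mechanism | -0.34 to -0.46 | 0.06 |
| 35% vs 15%, dependence on t0 or on t0-t1 change in one arm only | -0.29 to -0.51 | about 0.11 |
| Largest case at correlation 0.7 | | about 0.09 |

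In all of these scenarios, an estimator using t0 and t1 of every patient returned -0.40 within simulation error.

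**4. What this means for the test.** With 100 completers per arm and SD 1, the standard error is √(2/100) = 0.141. With no true effect, a bias b gives a two-sided error of 1 - Φ(1.96 - b/0.141) + Φ(-1.96 - b/0.141). That is about 6% for b = 0.05, 11% for 0.10 and 12% for 0.11, against the nominal 5%. As a share of the planned effect, 0.11 / 0.40 = 28%.

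**5. Where the remedy stops.** If dropout depends on the unseen t2 score itself, the t0/t1-based estimator was no better than complete cases and slightly worse: about -0.25 to -0.56 against -0.29 to -0.52. If dropout depends on the unseen t0-t2 change (separate run with no true effect, 15% vs 35%, log-odds 1), bias fell from about 0.16 to 0.09-0.11 SD of the change and was not removed.

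**The case against.** The strongest reply is that the article gives a single 25% rate and links it to a clinic where both arms had their MKP. A reader might infer from the unequal contact that dropout will differ between arms. The documents do not show that: extra contact could improve retention and training burden could worsen it, so neither a difference nor its direction is established. This part of the reply stands.

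The upper end of the range also needs several unfavourable assumptions together: correlation 0.5, a fairly strong dependence in one arm only, and a 20-point gap in dropout. Milder settings give 0.03 to 0.04 SD, roughly a quarter of a standard error. That also stands, and it is why the whole range is shown.

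A reader might also say that complete cases are valid only if dropout is unrelated to outcome, or related identically in both arms. That is too strong. Dropout driven by t1 alone, even in one arm only, left the change contrast unbiased when t1 correlated equally with t0 and t2.

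The covariate adjustment foreseen under Limitations helps in part. Complete-case adjustment for baseline PDQ-8 returned -0.40 in the t0-driven scenarios but stayed off by about 0.04 when dropout followed the response during MKP. That passage is aimed at drift between cohorts and does not name PDQ-8, so it is not a plan for dropout.

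Finally, leaving out 33 patients per arm is no shortfall in planned power, because the trial is sized on 100 completers per group. Nor does the rule reach the interviews, focus groups or cockpit data, which have their own analysis sections.

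**Conclusion.** The point holds as a conditional one. A stated rule confines all quantitative evaluations, including the primary 9-month comparison, to completers, although a quarter of patients are expected to be lost and contact and burden after MKP differ by arm. The comparison is open to attrition bias of unknown size and direction. Under the assumptions shown, the bias in the change contrast runs from 0 to about 0.11 SD when dropout depends on observed scores. These figures illustrate the exposure and do not forecast it.

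Two stronger conclusions are not supported: that the result will be biased, and that a mixed model or imputation would make it unbiased. Those methods remove the bias only if dropout depends on observed data. The case for change is that they use information already collected and cost little. This should be fixed, ideally before any t2 data are examined; it is not a fatal flaw.

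**What to change.** Replace the complete-case sentence with text such as:

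*The primary analysis includes every enrolled patient with a t0 PDQ-8, using a likelihood-based mixed model for repeated measures (t0, t1, t2) or multiple imputation by group using t0, t1 and baseline covariates. The complete-case analysis is a sensitivity analysis.*

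Choose one of the two methods in advance. Report retention and reasons for dropout by arm. Add a delta-adjusted sensitivity analysis that shifts the missing t2 values, with the shift allowed to differ by arm, because neither method protects against dropout that depends on the unobserved 9-month score.

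The cost is a change to the analysis text and a little more analysis work. It needs no extra patients, visits or questionnaires, and the sample size stays as it is. The downside is reliance on a missing-at-random assumption, which the delta analysis is there to test.
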